### 7.4. Sample size calculation

Using data from a previous non-randomized prospective study our group conducted a sample size calculation prior to conducting the present the randomized controlled trial. A two-sided log-rank test with an overall sample size of 190 subjects (95 in the TE group and 95 in the TO group) achieves 80.2% power at a 0.05 significance level to detect a TO median recovery time of 8 days when the TE group median survival time is 13.5 days within a 14-day total observation time.

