## 7. Methods

### 7.1. Primary endpoint

- Number of days post-operative recovery to resumption of daily activities

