### 7.3. Randomization

After informed consent, the patient will be randomized to one of the two treatments. It is not possible to perform the study blinded. The drawing will be done by means of a stratification randomization, taking into account the indication. About 50% of the patient group will be randomized to a classic tonsillectomy and about 50% to a laser tonsillotomy.

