### 7.5. Study procedure

To evaluate the primary and secondary outcome measures, the patient will be asked to complete a digital evaluation form preoperatively, 2 weeks, 6 months, 1 year and 2 years after the procedure (follow-up study). These forms will be offered by e-mail. In the event of recurrent complaints after the procedure, the patient is asked to go to the ENT doctor /

general practitioner for assessment and to report this to the investigator (by telephone / email). This will also be re-evaluated in the fixed measurement moments.

The operator will fill in a number of questions related to the procedure.

Laser procedure:

- Duration of the laser procedure
- Total duration of outpatient visit
- Amount of local anesthesia administered (number of cartridges)
- Pain during the procedure (VAS score) (patient perception)
- Use of supplemental anesthetic, and the amount thereof
- Coagulation required / not required during procedure
- Complications during surgery

Classic TE procedure:

- Duration procedure (cutting time)
- Duration of hospitalization
- Pain relief administered during surgery (medication, dosage)
- Pain related to procedure (injecting an IV, etc.) (VAS score) (perception pt)
- Coagulation required / not required during procedure
- Complications during surgery

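### The 14-day observation time ends half a day after the assumed tonsillectomy median, so the difference in recovery days often cannot be estimated; extending it to day 28 is a cheap improvement

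*Protocol*

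**What the plan says.** Section 7.1 defines the primary endpoint as "Number of days post-operative recovery to resumption of daily activities", and section 8.2 compares it by survival analysis. Section 3 states the hypothesis in days: recovery after the laser procedure should differ from classic tonsillectomy by at least 3.

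Section 7.4 gives the design basis. The planned comparison is "A two-sided log-rank test with an overall sample size of 190 subjects", split equally between the arms. Its power is put at 80.2% with alpha 0.05, on the assumption that half of the TO patients recover by day 8. The control assumption and the length of follow-up appear together in one clause: "when the TE group median survival time is 13.5 days within a 14-day total observation time". Section 7.3 confirms roughly equal allocation.

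Section 7.5 asks patients to "complete a digital evaluation form preoperatively, 2 weeks, 6 months, 1 year and 2 years after the procedure". After the 2-week form the next contact is therefore at 6 months. The protocol gives no reason for the 14-day limit and does not say that recovery dates after day 14 will be collected for the primary outcome.

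**The concern.** The assumed TE median and the end of observation are half a day apart. By definition about half of the control arm will not have recovered when observation stops, and for those patients the record reads only as more than 14 days. A Kaplan-Meier median can be read off only if the curve falls to 50%. Here it is expected to end almost exactly there, so chance decides whether a TE median exists.

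The endpoint is a number of days and the hypothesis is a difference in days. The trial could return a significant log-rank p-value and still be unable to give the TE median, its confidence interval or the difference between medians. A statistical analysis plan cannot repair this later if the dates were never collected.

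**Working it through.** **Inputs.** From section 7.4: medians 8 days (TO) and 13.5 days (TE), 95 per arm, two-sided 0.05, observation to day 14. Assumptions of this check: exponential recovery times (the protocol names no distribution), every patient observed to day 14, and no dropout (none is stated).

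**1. Reproduce the stated power.** Probability of recovery by day t is 1 − 2^(−t/median).
- TO: 1 − 2^(−14/8) = 0.703
- TE: 1 − 2^(−14/13.5) = 0.513
- Expected events: 95 × (0.7027 + 0.5127) = 115.5
- Log hazard ratio: ln(13.5/8) = 0.523
- Schoenfeld: √115.5 / 2 × 0.523 = 2.81; Φ(2.81 − 1.96) = 80.3%

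The protocol states 80.2%, so its figure is reproduced. A simulated log-rank test on whole days (2,000 runs) gave 80.0%. The agreement also shows that the stated power already allows for censoring at day 14.

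**2. Censoring at day 14.** TE: 1 − 0.513 = 48.7%, about 46 of 95. TO: 1 − 0.703 = 29.7%, about 28 of 95.

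**3. Chance that the TE median is not reached.** With 95 patients the curve reaches 50% only if at least 48 recover. P(Bin(95, 0.513) ≤ 47) = 40.2%. The upper 95% limit for the TE median is missing in about 95% of trials (94.6% with a log-log interval, about 96% with an order-statistic approximation).

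**4. Dependence on the exponential model.** Weibull times with the same medians, recovery probability 1 − 2^(−(t/median)^shape):

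| Shape | TE unrecovered at day 14 | P(TE median not reached) |
|---|---|---|
| 1 | 48.7% | 40% |
| 1.25 | 48.4% | 38% |
| 1.5 | 48.1% | 35% |
| 2 | 47.5% | 31% |
| 3 | 46.2% | 23% |

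The estimation problem persists throughout, because observation ends close to the median whatever the shape.

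**5. A longer window, same 190 patients (exponential, Schoenfeld).**

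| Censoring day | Events | Power | TE censored | P(TE median not reached) |
|---|---|---|---|---|
| 14 | 115.5 | 80.3% | 49% | 40% |
| 21 | 142 | 87.7% | 34% | 0.07% |
| 28 | 159 | 91.0% | 24% | about 0 |
| none | 190 | 95.0% | 0% | 0 |

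**6. The power gain under a rising hazard.** Power at 14 and 28 days is 80.3% and 91.0% at shape 1, 94.8% and 98.9% at shape 1.25, and 99.3% and 99.9% at shape 1.5. The gain falls from about 11 points to about 4, then to under 1.

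**The case against.** **Follow-up beyond day 14 is not ruled out.** The 14-day figure appears only in the sample-size sentence. Section 7.5 introduces all the forms as serving both primary and secondary outcomes, sections 7.1 and 8.1 put no cap on recovery days, and section 8.2 names no censoring day. The 6-month form might ask for a later date. This stands in part: a reader might infer that the protocol expressly ends follow-up for the primary endpoint with the 2-week form, but that is an inference from the sample-size sentence and the form schedule. What can be said is that the only stated observation time is 14 days and that later collection is not provided for.

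**Nothing is miscalculated.** This stands in full. A reader might infer that the trial is underpowered or its test compromised. Neither follows: 80.2% is right for the stated window, and censoring at a common day leaves the log-rank test valid. An unreached median could be reported as more than 14 days, with the curves, the proportion recovered by day 14 and a hazard ratio. That limits the harm but does not give a difference in days.

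**The power gain depends on the model.** This stands: 11 points at day 28 is the constant-hazard figure, and step 6 shows how quickly it shrinks.

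**The 3-day hypothesis.** A reader might compare mean recovery restricted to 14 days between arms (a difference of 1.9 days under the exponential model) with the 3 days in section 3 and conclude that the hypothesis cannot be met. The protocol does not support this. It nowhere uses a restricted mean, such a mean is compressed by construction, and the planning difference is 13.5 − 8 = 5.5 days in medians.

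**Conclusion.** The point holds as a cheap improvement to the design, not as an error that must be corrected. On the plan's own medians, just under half of the TE arm (46% to 49% over Weibull shapes 3 to 1) is unrecovered at day 14, and the TE median is not reached in 23% to 40% of trials. This rests on the planning medians being right, no dropout, and no recovery dates after day 14 entering the primary analysis. It depends little on the shape of the distribution.

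The efficiency loss is secondary and less certain, since it also assumes that the planning model continues to hold beyond day 14.

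**What to change.** - **Data collection (section 7.5).** Patients who report on the 2-week form that they have not resumed daily activities receive a one-question e-mail weekly to day 28. The 6-month form asks for the date only if it is still missing, as a backstop.
- **Analysis (section 8.2).** Censor the primary analysis at day 28.
- **Sample size (section 7.4).** Keep 190 patients, and restate the power for the 28-day window together with the distribution assumed: about 91% if exponential.

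The cost is a short amendment, one automated question (forms already go by e-mail) and slight patient burden. Any date first given at 6 months carries recall error, which matters more because the trial is unblinded and the outcome is reported by the patient. The weekly e-mails should therefore be the main source. The change should be made before patients pass the 2-week form, since dates missed then are hard to recover reliably.

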### 7.5. Study procedure

To evaluate the primary and secondary outcome measures, the patient will be asked to complete a digital evaluation form preoperatively, 2 weeks, 6 months, 1 year and 2 years after the procedure (follow-up study). These forms will be offered by e-mail. In the event of recurrent complaints after the procedure, the patient is asked to go to the ENT doctor /

general practitioner for assessment and to report this to the investigator (by telephone / email). This will also be re-evaluated in the fixed measurement moments.

The operator will fill in a number of questions related to the procedure.

Laser procedure:

- Duration of the laser procedure
- Total duration of outpatient visit
- Amount of local anesthesia administered (number of cartridges)
- Pain during the procedure (VAS score) (patient perception)
- Use of supplemental anesthetic, and the amount thereof
- Coagulation required / not required during procedure
- Complications during surgery

Classic TE procedure:

- Duration procedure (cutting time)
- Duration of hospitalization
- Pain relief administered during surgery (medication, dosage)
- Pain related to procedure (injecting an IV, etc.) (VAS score) (perception pt)
- Coagulation required / not required during procedure
- Complications during surgery

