**Complications of laser treatment:**

- About 10% have not gotten rid of the complaints and have so many complaints that they undergo a classic dissection tonsillectomy
- In total, about 20% of patients undergo more than 1 laser treatment
- wound infection (3.4%)
- Bleeding requiring intervention (<1%)
- Allergic reaction to the local anesthetic (<1%)
- Side effects of the anesthetic (xylocaine 2% / adrenaline 1: 80,000) as described in the package insert (<1%)

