## 8.2. Analysis

All analyzes will be performed with an intention-to-treat analysis.

A two sided p value  $<0.05$  will be considered significant for all analyses. Survival analysis will be used to compare the primary outcome of recovery time. Survival analysis will also be used to compare time to return to work and postoperative analgesic use. Secondary outcome measures on a continuous scale will be compared using unpaired T-tests or Mann-Whitney U tests, depending on the normality of data (tested using Shapiro-Wilk test). Proportions will be compared using Fisher exact tests.

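### Follow-up forms are triggered only by the operation, so randomised patients who are never operated on have no scheduled long-term outcome, which does not fit the stated intention-to-treat analysis

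*Protocol*

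**What the plan says.** Section 7.5 makes the e-mailed forms the source of the trial's outcomes: "To evaluate the primary and secondary outcome measures, the patient will be asked to complete a digital evaluation form". It times them by asking the patient to "complete a digital evaluation form preoperatively, 2 weeks, 6 months, 1 year and 2 years after the procedure". No patient form in the text is dated from randomisation. The only other reporting route in 7.5, for recurrent complaints, also applies after the procedure.

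Section 7.3 places the draw after consent: "After informed consent, the patient will be randomized to one of the two treatments". On masking it says: "It is not possible to perform the study blinded". Section 8.2 sets the analysis principle without exception: "All analyzes will be performed with an intention-to-treat analysis".

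The primary endpoint in section 7.1 is "Number of days post-operative recovery to resumption of daily activities". The secondary endpoints in sections 3.1.2 and 7.2 include presence of the tonsil-related complaint, yearly tonsillitis episodes, yearly antibiotic courses and yearly absence days. Section 7.6 lets a patient withdraw at any time. It does not separate declining the operation from leaving follow-up, and it describes no continued follow-up.

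**The concern.** Intention to treat needs outcomes sought from everyone randomised. Under section 7.5 a patient without an operation date has nothing from which a follow-up form can be counted. Statistical analysis plans can say how missing values are handled, but they cannot recover data that the schedule never asks for.

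Such patients are foreseeable. Allocation is open, and the two arms are very different for the patient: outpatient laser under local anaesthesia at one hospital, or general anaesthesia with an admission at the enrolling centre (sections 4.1, 6.1, 6.2). Section 9.2 says conservative treatment is discussed before consent. A patient may decline after an unwelcome draw, or improve while waiting, and either could occur at different rates in the two arms. The long-term effectiveness comparison would then be made in groups selected after randomisation.

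**Working it through.** **1. Which outcomes are affected.** Setting the schedule beside the endpoints:

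| Outcome | Defined without surgery? | Form scheduled if never operated on? |
|---|---|---|
| Days of recovery (7.1) | No | No |
| Sick leave in the year following surgery (7.2) | No | No |
| Tonsil-related complaint present or absent | Yes | No |
| Tonsillitis episodes, antibiotic courses, absence days per year | Yes | No |

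The last two rows carry the conflict: the outcome exists for every randomised patient, but it is collected only from operated ones. In the first two rows the outcome itself needs an operation, so the issue there is how the analysis set is described.

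**2. Who is affected.** Section 7.5 counts from the procedure, not from the allocated procedure. A patient who crosses over still has an operation date, receives every form, and can be analysed in the allocated arm. Only patients who have no operation fall out.

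**3. Size of a possible bias in a yes/no outcome.** In one arm let d be the fraction not operated on, p the complaint-free proportion among the operated and q that among the unoperated. The proportion in all randomised patients is (1 − d)p + dq. The operated-only figure differs from it by

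p − [(1 − d)p + dq] = d(p − q),

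which lies between −d and +d. The bias in the comparison is d_TE(p_TE − q_TE) − d_TO(p_TO − q_TO). It is zero if d and p − q are the same in both arms. The protocol gives no value for d or q. The previous series in section 2 (425 patients) consists of patients who had the laser procedure, so it cannot supply d. For an assumed d of 5% to 10%, the limit within an arm is 5 to 10 percentage points in either direction.

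**4. Primary endpoint.** Section 7.4 gives 95 per arm, medians of 13.5 days (TE) and 8 days (TO), 14 days of observation, two-sided 0.05 and 80.2% power. With exponential recovery times:

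- Hazard ratio = 13.5/8 = 1.6875; its logarithm is 0.5232.
- Recovered by day 14: 1 − 2^(−14/13.5) = 0.513 (TE) and 1 − 2^(−14/8) = 0.703 (TO).
- Expected events = 95 × 0.5127 + 95 × 0.7027 = 115.5.
- Schoenfeld power = Φ(√115.46/2 × 0.5232 − 1.96) = Φ(0.851) = 80.3%.

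The stated 80.2% is reproduced, and it takes all 190 patients as contributing recovery data. With an assumed equal fraction unoperated in both arms, the same formula gives:

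| Unoperated (assumed) | Per arm | Expected events | Power |
|---|---|---|---|
| 0% | 95 | 115.5 | 80.3% |
| 5% | 90 | 109.4 | 78.1% |
| 10% | 86 | 104.5 | 76.3% |
| 20% | 76 | 92.4 | 71.0% |

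The loss of power is modest at 5% to 10%. The follow-up fix does not change it, because unoperated patients have no recovery time.

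**The case against.** The strongest reply is that the operation is the natural origin in a surgical trial. For recovery time this is right: dating it from randomisation would add waiting time to it. Analysis by allocated arm also works for every operated patient. Both points stand, and they limit the finding to patients never operated on.

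A reader might go further than the protocol supports in four ways.

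- **Baseline after allocation.** The text does not fix the order of the preoperative form and the draw. Section 1 refers to the flow chart for measurement moments, and that figure is not shown in the available text. A baseline reported with knowledge of the arm is permitted by the wording but not established. Section 8.2 names no baseline-adjusted comparison that it would distort.
- **All long-term forms should be dated from randomisation.** This is a trade-off, not a correction. It would not match the endpoint on sick leave in the year following surgery. If waits differ by arm, it would give the arms unequal time since surgery at each form. The protocol states no waiting times.
- **Repeat laser leaves no single clock.** Section 1 says "In total, about 20% of patients undergo more than 1 laser treatment", but the procedure in 7.5 is naturally the first operation, and section 8.1 lists the number of sessions and later tonsillectomy as outcomes. A clarifying sentence is enough.
- **A ten-point bias against the 30% in section 3.** Suppose 10 of 95 tonsillectomy patients are unoperated and 81 of the 85 operated are complaint-free (95.3%). If all ten still have complaints, the figure is 81/95 = 85.3%, a gap of 10.0 points. If all ten have improved, it is 91/95 = 95.8%, a gap of 0.5 points the other way. The first figure is an assumed one-arm worst case, and section 8.2 specifies no test against the 30%.

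**Conclusion.** The concern holds in a limited form. As written, section 7.5 schedules no 6-month, 1-year or 2-year form for a randomised patient who is never operated on, and this does not fit the intention-to-treat statement in section 8.2 for the long-term secondary outcomes that have meaning without surgery. The primary recovery analysis can include only operated patients because of how its endpoint is defined, and 8.2 should say so.

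The size and direction of any bias are unknown, because the protocol gives neither a rate of unoperated patients nor their outcomes. The 5% to 20% used for power is an assumption. No stated figure is wrong on this point. The conclusion rests on the protocol text: it would fall away if the flow chart schedules long-term forms for unoperated patients, but nothing in the text indicates that.

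**What to change.** In section 7.5:

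- Send the 6-month, 1-year and 2-year forms to every randomised patient, operated on or not.
- Keep the first study operation as the time origin for operated patients. Use a fixed substitute, for example the date of randomisation, for those not operated on.
- State that the clock does not restart at a repeat laser session or a later tonsillectomy.
- Keep the 2-week recovery form dated from the operation.
- Unless the flow chart already does so, state that the baseline form is completed after consent and before the draw.

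In section 8.2:

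- Describe the primary recovery analysis as randomised and operated patients, by allocated arm.
- Report, per arm, the number not operated on and the wait from randomisation to surgery.

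The cost is a few extra e-mailed forms, a second date trigger in the data system and some sentences of text. The downside is a time origin that differs for the unoperated patients, expected to be few. The sample size and the stated power calculation need no change for this.

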#### 7.6. Leaving the study prematurely

The patient can withdraw from the study at any time. The physician may withdraw the patient from the study at any time for medical reasons on the patient's behalf.

#### 7.7. Intervention prematurely / prematurely

Both the physician and the patient can decide during the procedure to terminate the intervention for medical or other reasons.

## Safety Considerations

### 7.8. Section 10 WMO

In accordance with section 10, subsection 4 of the Medical Scientific Research with Human Subjects Act (WMO), the sponsor will discontinue the study if there is a sufficiently substantiated suspicion that continuation of the study will endanger the health or safety of the patient. The sponsor will, without undue delay, inform the accredited MREC of the temporary discontinuation and the reason for stopping the study. The study will be discontinued pending a future positive decision from the accredited MREC. The researcher will ensure that all involved are informed.

### 7.9. Adverse events (AE) and serious adverse event (SAE)

With both treatments there is a risk of subsequent bleeding during the procedure or postoperatively. In the case of the classic TE, this is approximately 1.4% (2007) in the HAGA hospital where intervention is required. There is also a risk of infection after the treatment with both treatments, this risk is comparable for both interventions.

At present, there is no evidence that transmission of "transmissible spongiform encephalitis" can occur through inhalation of the smoke and / or vaporized tissue. In theory, however, there is a risk for this with CO2 laser tonsillotomy. Despite the fact that there are no specific guidelines for plumes of smoke in relation to variant Creutzfeld Jacob Disease and the risk of contamination of the treating physician and operating assistants is estimated to be very low, the safety guidelines regarding laser treatment recommend the use of an efficient filtering evacuation system. [14, 16]

Administration of local anesthesia may result in anaphylactic shock or a systemic reaction as described in the side effects of xylocaine / adrenaline.

In connection with these potentially unwanted consequences / side effects of the treatment, several precautions will be taken.

- An on-call ENT specialist is available at all times when a complication occurs that requires re-intervention / evaluation.
- Patient saturation and heart rate are monitored throughout the procedure.
- The procedures will take place in clinics where staff with BLS certificates will be present at all times. An anaphylactic set and respiratory equipment will also be available.
- The treatment room where the laser treatment takes place meets the criteria as formulated in the book "laser safety in health care" ([www.laserveiligheidindegezondheidszorg.nl](http://www.laserveiligheidindegezondheidszorg.nl)).

If there is an (S)AE, this will be reported via the ToetsingOnline web portal to the accredited MREC that has approved the protocol. If there is an SAE, this will be reported to the accredited MREC within 15 days. Death or life-threatening condition will be reported to the Medical Ethics Committee within 7 days and initial reporting will be completed within 8 days.

An annual safety report with an overview of all SAEs will be sent to the MREC.

